## Abstract

**Background:**

Effective communication skills are fundamental for health care professionals, yet conventional training methods face challenges in scalability and accessibility due to resource constraints. The emergence of artificial intelligence (AI), particularly generative AI, offers innovative ways for enhancing communication skills training by simulating realistic conversational scenarios and providing personalised, adaptive feedback. This manuscript is presented as study protocol for a cluster-randomised controlled trial that aims at evaluating the efficacy of an AI-supported higher education training protocol incorporating generative AI exercises to enhance communication competencies among psychology students.

**Methods:**

In this cluster-randomised controlled trial, psychology students enrolled in communication skill seminars at a medium sized university in a medium sized German city will participate. Classes will be assigned within a parallel group design to the AI condition (AI-enhanced exercises alongside teaching-as-usual, TAU, that includes classical exercises) or the control condition (TAU only). Additional non-randomised comparison classes will comprise students with TAU only, but not be part of main analyses. The primary outcome is the change in communication skills from baseline, assessed through questions reflecting the communication techniques emphasised in the training. Secondary outcomes include communication skills, self-efficacy and self-concept, motivation, attitudes toward AI, user experience with the AI tool, student evaluations of course quality, and feasibility aspects such as uptake and usability. Data will be collected via online surveys and the university’s teaching platform. Statistical analyses will employ mixed models to evaluate the intervention’s impact.

**Discussion:**

This study will provide empirical evidence on the effectiveness and feasibility of integrating AI into higher education communication skills training. Successful integration of AI-enhanced training could revolutionise educational practices by offering scalable, accessible, and personalised learning experiences. The findings may have broader implications for incorporating AI tools in various educational and professional training contexts, while addressing ethical considerations and promoting responsible use of AI in education.

**Trial registration:**

This trial has been pre-registered on the Open Science Framework (OSF) under identifier ‘th6f4’.

**Supplementary Information:**

The online version contains supplementary material available at 10.1186/s12909-025-07307-3.

## Background

Effective communication skills are fundamental for professionals in health and psychology, underpinning successful client interactions, therapeutic alliances, and overall intervention efficacy [1]. Proficient communication enables accurate assessment, enhances client engagement, and contributes to positive treatment outcomes. Traditionally, communication skills training for psychology students involves in-person seminars, role-playing exercises, and supervised clinical interactions. While these methods are valuable, they often require substantial time, resources, and access to trained facilitators, potentially limiting scalability and accessibility.

The advent of artificial intelligence (AI), particularly generative AI, including large language models (LLMs), such as Generative Pre-trained Transformer 4 (GPT-4), offers innovative avenues for enhancing communication skills training. These AI technologies can simulate realistic conversations, provide instant feedback, and adapt to individual learning needs, thereby offering accessible, flexible, and personalised learning opportunities [2, 3]. The coronavirus disease 2019 pandemic accelerated the adoption of digital learning tools, highlighting the potential of AI to maintain educational continuity and support remote learning, even in complex skill domains like communication [4]. However, while LLMs offer new opportunities for interactive, personalised learning experiences, their integration into education requires careful consideration. Recent discussions highlight that both educators and learners must develop new literacies and competencies to effectively and ethically use these tools [5]. This includes recognising potential biases, ensuring human oversight, and fostering critical thinking and fact-checking skills when engaging with AI-generated content.

Emerging evidence suggests that AI-enhanced communication skills training can be effective in healthcare education. Stamer et al. [6] conducted a scoping review highlighting the use of AI and machine learning applications in communication training, including text analysis and virtual patient simulations. These technologies have been shown to provide individualised feedback and increase accessibility and cost-effectiveness of training programs. However, limitations such as the lack of authenticity and natural language flow in AI interactions were noted. Kobayashi et al. [7] evaluated a multimodal communication skills training program for physicians that included AI-based video analysis. The study found significant improvements in physicians’ communication skills, empathy, and reductions in burnout scores post-training, indicating the potential benefits of integrating AI in clinical communication training. Similarly, an AI-enabled virtual reality simulation improved interprofessional communication knowledge and self-efficacy among nursing students, although the AI’s human-like features received lower ratings, suggesting areas for enhancement [8]. In the context of psychological interventions, a ‘ClientBot’ in form of a patient-like conversational agent that provided real-time feedback to trainees on their use of basic counselling skills demonstrated significant improvements in trainees’ use of reflections and listening skills compared to those who did not receive AI feedback [9]. Emerging evidence indicated that the use of virtual standardised patients for mental health education with AI-driven tools supported experiential learning and skill transfer to real clinical settings [10]. These approaches align with evidence from simulation-based learning research in higher education. Meta-analytic findings indicate that simulations are among the most effective means to facilitate the learning of complex skills across domains, with technology-based and scaffolded simulations showing robust positive effects on learning outcomes [11]. Integrating AI-driven simulations into communication training may build upon these effective instructional strategies.

Despite these promising findings, there are notable challenges in implementing AI-based communication training. First, the authenticity of interactions can be limited if the AI’s generated text fails to capture the nuance of human responses or emotional expressions [12]. This can be addressed, for example by regularly comparing AI outputs with human-generated responses in similar scenarios and refining prompts to improve contextual and emotional relevance [13]. Second, managing biases is paramount, as large language models may inadvertently reproduce societal biases inherent in the training data [14]. This can be mitigated by a structured prompt-design process, which includes iterative review and monitoring for unintended or biased content and guide prompt modifications [14]. This approach allows to refine, when necessary, how the model is prompted, ensuring more equitable and accurate outputs. Third, technical constraints – including the stability of the platform and the need for real-time feedback – require robust system monitoring. This can be addressed by periodically sampling transcripts to detect anomalies and refine prompts [15]. Given these challenges, a rigorous, empirically grounded evaluation – such as our cluster-randomised controlled trial – is essential to test both the effectiveness and the feasibility of AI-supported communication skills training under real-world conditions. This evaluation will provide critical insight into whether the potential benefits of AI-based training – improved scalability, individualised feedback, and consistent practice opportunities – can be realised without compromising authenticity, fairness, or technical reliability.

This manuscript is presented as a prospective study protocol for a cluster-randomised controlled trial. No participant data have been collected at the time of writing, as our primary aim is to provide a transparent overview of the study’s objectives, design, intervention strategies, and planned analyses. Protocol papers offer an opportunity for peer review of the proposed methodology prior to data collection, thereby strengthening the quality and reproducibility of the forthcoming research.

The presented cluster-randomised controlled trial aims at evaluating the efficacy of an AI-supported training protocol that incorporates communication skills training exercises powered by generative AI. The intervention focuses on enhancing communication competencies among psychology students, using AI to support and expand conventional seminar methods.

Communication competencies involve not only the demonstration of specific conversational techniques but also the psychological determinants underlying skill acquisition and performance. Research in educational psychology indicates that self-efficacy (i.e., confidence in one’s ability to perform a task) and a positive self-concept in a given domain can significantly predict persistence, engagement, and actual skill performance [16]. Similarly, motivation and attitudes, including attitudes toward new technologies such as AI, can influence the degree of effort and openness a learner devotes to improving communication skills [17]. Accordingly, our study includes measures of self-efficacy, self-concept, motivation, and AI-related attitudes to illuminate potential mediating or moderating factors that may enhance or impede the development of communication competencies.

By integrating AI-based tools into training programs, we aim to enrich the educational experience, making it more accessible and adaptable to individual needs. This initiative aligns with the growing body of research advocating for the integration of AI in educational and training contexts, especially in health-related fields.

The primary objective of this study is to determine whether integrating AI into communication skills training enhances the communication competencies of psychology students more effectively than conventional methods. Specifically, we aim to: i) assess the improvement in communication skills among students who participate in AI-enhanced exercises compared to those undergoing standard seminar training; ii) evaluate the impact of AI-enhanced training on students’ communication skills self-efficacy and self-concept, motivation, attitudes toward AI and communication, and the student evaluations of the course quality; iii) examine the uptake, usability, and user experience of the AI tool within the context of communication skills training; iv) assess the feasibility and implementation aspects of incorporating AI-based communication skills training in an educational setting.

Thereby, our hypotheses (H) are as follows: H1: Receiving AI-enhanced communication skills exercises will be linked to greater improvements in communication skills compared to receiving conventional teaching methods only. H2: Receiving AI-enhanced communication skills exercises will be linked to higher levels of reported communication skills self-efficacy and self-concept, motivation, more positive attitudes toward AI, and more positive student evaluation of the course quality than receiving conventional training. H3: The AI tool will be deemed highly usable and will provide a positive user experience, as reported by participating students. H4: The uptake of AI-enhanced communication skills exercises will be higher than uptake of conventional communication skills exercises, demonstrating acceptance of integrating AI into communication skills training programs.

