**Fig. 1 Fig1:**
[figure not shown]
Study design. Notes: Classes follow a parallel group design (randomised to Clusters Type A vs. B: AI condition vs. TAU only). Cluster Type C represents optional, non-randomised classes that can serve as observational comparators and are not part of main analyses. Abbreviations: AI, artificial intelligence; CSS, communication skills seminar; TAU, taught as usual

In the parallel group design, classes are randomised to the AI condition (Cluster Type A, with Condition 1 only: AI-enhanced exercises alongside teaching-as-usual, TAU, that includes classical exercises) or the control condition (Cluster Type B, Condition 2: TAU only). Additional non-randomised comparison classes (Cluster Type C, Condition 3) will comprise students with TAU only but not be included in the main analyses.

Details regarding the Conditions are as follows:

In Condition 1 (Intervention with AI-enhanced exercises alongside TAU), Participants will use AI-enhanced communication skill exercises provided via the HAWKI platform alongside TAU, in the context of the standard communication skills seminar, which includes not-AI-enhanced communication skills exercises. HAWKI is a data protection-compliant platform that serves as a wrapper for OpenAI's ChatGPT. HAWKI is web-based and grants access to state-of-the-art language models (currently GPT-4o), made available through university accounts to protect personal log-in data. It thereby allows users to interact with ChatGPT without requiring personal account creation with OpenAI, thereby enhancing user privacy and aligning with General Data Protection Regulation (GDPR) standards. Students receive access to HAWKI and instructions for its use through the online learning platform ‘Stud.IP’. The exercises will involve AI-facilitated interactions designed to simulate real communication scenarios. Students will follow structured system prompts tailored to improve their communication skills. This condition will be implemented for the full duration of the seminar. The content of the intervention is described in more detail below.

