During times where Condition 2 (first comparator, TAU only) is active, participants will attend the standard communication skills seminar, which includes not-AI-enhanced communication skills exercises. This condition will be implemented for the full duration of the seminar within the semester lecture period, with participants getting no specific access to AI tools or related prompts outlined in Condition 1.

Participants undergoing Condition 3 (second, non-randomised comparator, TAU only) will attend communication skills seminar with instructions and exercises comparable to those in Condition 2. This Condition will serve as an observational, non-randomised control to compare against condition 1, but not be part of the main analyses. It is added due to procedural reasons in cases where randomisation of a seminar to Conditions 1 or 2 is not feasible. This may occur for example if certain classes already began instruction before randomisation could take place or if they are run by instructors who cannot accommodate the required arrangement. Such classes serve as an additional, observational comparator to explore potential baseline or contextual differences. We will address these differences by adjusting for key covariates (e.g., baseline skill levels) in the analyses.

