The curriculum for the intervention includes a series of distinct AI-enhanced communication skills exercises. Students are encouraged to complete each exercise to reinforce their learning and ensure proficiency in the communication skills being trained. During the designated training periods, students may engage in an unlimited number of exercises, allowing for flexible, self-directed learning tailored to their individual needs and schedules. The exercises shall allow repeated practice and receiving iterative feedback from the AI, enhancing the learning process. The students will receive regular notifications to inform them about the next set of exercises that is consecutively made available during the phase at which condition 1 is implemented. This approach is designed to maximise the accessibility and effectiveness of the training, adapting to the diverse learning preferences and requirements of the students.

Currently, HAWKI supports text-based interactions only, and no voice functionality is available within the university’s data-protected wrapper. Therefore, all AI exercises in this study will be text-based for consistency. If future HAWKI updates enable secure audio or multimodal exchanges, we may explore those in a separate follow-up investigation; they will not be part of the main RCT described here.

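### Higher uptake of add-on AI exercises would not by itself show acceptance, and adding AI to TAU cannot show that AI beats conventional practice

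*Protocol article*

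**What the plan says.** **Arms (Study design).** Condition 1 is "AI-enhanced exercises alongside teaching-as-usual, TAU, that includes classical exercises". Condition 2 is the standard seminar alone, "with participants getting no specific access to AI tools or related prompts outlined in Condition 1". No extra practice of matching volume is described for Condition 2.

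**Supply of AI exercises (Description of AI-based communication skills exercise).** During the training periods "students may engage in an unlimited number of exercises, allowing for flexible, self-directed learning". On prompting: "The students will receive regular notifications to inform them about the next set of exercises that is consecutively made available". After each set of interactions, students must copy the transcript into Stud.IP.

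**H4 (Background).** "The uptake of AI-enhanced communication skills exercises will be higher than uptake of conventional communication skills exercises, demonstrating acceptance of integrating AI".

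**Objective (Background).** The trial is to determine "whether integrating AI into communication skills training enhances the communication competencies of psychology students more effectively than conventional methods". The opening of the Discussion repeats the comparison with conventional methods. H1 is more careful: its comparator is conventional teaching on its own, and the Background describes AI as supporting and extending the seminar.

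**Measurement (Table 1).** Exercise volume, both total and AI-only, is recorded at T1 in the AI and control classes, from student report and from Stud.IP. The System Usability Scale and group feedback on AI use are planned in the AI classes. Student evaluation of the skills practice is planned in all classes.

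**The concern.** Two conclusions are written into the hypotheses and objectives that the design does not support.

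First, H4 reads a higher uptake figure for AI as evidence of acceptance. Uptake depends on how much is offered, how often students are reminded of it and how completely it is recorded, as well as on whether they want it. H4 does not say whether the comparison is within the AI arm or between arms, nor whether uptake is a count, a duration or a share of what was offered.

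Second, the objective sets AI against conventional methods, while the arms differ by an addition, not a substitution. A positive result could be reported as AI outperforming conventional training when more practice of any kind might explain it as well.

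At stake is what the trial may conclude. The validity of its randomised comparison is not in question.

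**Working it through.** No figure in the protocol tests this point. It gives neither the number of conventional exercises offered nor the number of AI sets. The values below are assumptions that show the mechanism; they are not estimates.

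**1. What H4 could be comparing**

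- Within the AI arm: AI exercises against conventional exercises done by the same students. Both types are available, but the protocol describes unlimited supply, notifications and transcript upload for the AI type only. It does not say how the conventional type is supplied.
- Between arms: AI uptake in Condition 1 against conventional uptake in Condition 2. Control students are given no specific access to the AI tools, so who can show AI uptake is largely settled by allocation.

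Neither reading isolates acceptance.

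**2. Count ratio at equal acceptance**

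Let students complete the same share p of whatever is offered, with C conventional and A AI exercises offered. Then the ratio of counts = pA / pC = A / C, whatever p is. With p = 0.5 and C = 10:

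- A = 10: 5 against 5, ratio 1.0
- A = 15: 7.5 against 5, ratio 1.5
- A = 20: 10 against 5, ratio 2.0

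The share completed is 50% for both types throughout. The reverse also holds: with C = 20 and A = 10 the counts are 5 AI against 10 conventional, ratio 0.5. The count follows the offer in either direction, so a high ratio does not establish acceptance and a low one does not refute it.

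**3. Between-arm difference if only practice volume mattered**

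Suppose AI practice is worth exactly as much as conventional practice, so that the AI-specific effect is zero. Let g be the gain in SD units from one course's volume of practice, and e the extra volume in the AI arm as a fraction of the control arm's volume. The difference between arms is d = g × e.

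The protocol's target is at least 50 per condition. With SD 1, two-sided alpha 0.05 (the protocol gives 0.05 but not the sidedness) and no clustering, the chance of a significant result favouring AI is approximately Φ(d√(50/2) − 1.96) = Φ(5d − 1.96).

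- g = 0.25, e = 0.25: d = 0.0625, chance 5.0%
- g = 0.25, e = 0.5, or g = 0.5, e = 0.25: d = 0.125, chance 9.1%
- g = 0.25, e = 1.0, or g = 0.5, e = 0.5: d = 0.25, chance 23.9%
- g = 0.5, e = 1.0: d = 0.50, chance 70.5%

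Clustering lowers these chances. For the last case, assume 10 students per class and an intraclass correlation of 0.01 to 0.10. The design effect is then 1 + 9 × ICC = 1.09 to 1.9, and the chance is 66.8% to 44.2%. The size of d does not change.

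Under these assumptions volume alone produces a difference of about 0.06 to 0.50 SD. A positive result would be compatible with extra practice alone, and equally with an AI-specific effect.

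**4. Whether the planned analyses resolve this**

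Methods for additional analyses relates exercise intensity to outcomes. Intensity arises after randomisation and is chosen by the student, so those associations cannot separate AI from practice volume in the way a randomised contrast could.

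**The case against.** The strongest reply is that the add-on comparison is already declared. H1 names conventional teaching alone as the comparator, the arms are clearly defined, and the objective speaks of integrating AI. Extra opportunity to practise is one of the benefits the Background attributes to AI, so it belongs to the intervention and is not an outside confounder. This stands. The primary contrast matches its hypothesis, and wanting an equal-volume control would be a different research question. What remains is that the objective and the Discussion use broader wording than H1.

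A reader might go further and infer that the trial measures extra supply and not AI, or that H4 is bound to be confirmed. The documents do not support either inference:

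- The randomised comparison estimates the combined effect of adding AI exercises, which is not supply alone.
- The protocol never says that conventional exercises are capped, unannounced or unrecorded. Table 1 in fact records total volume in both arms, including through Stud.IP.
- H4 could fail. Conventional exercises are built into the seminar, AI exercises are only encouraged, and copying transcripts is a burden that could lower registered AI uptake.

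It can also be said that the uptake metric belongs in an analysis plan. That is fair for the metric. The step from higher uptake to acceptance, however, is written into the hypothesis, and no later choice of a count would make it sound.

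**Conclusion.** The point holds in a limited form. H4's acceptance inference is unsound as written, because supply and prompting can raise the AI figure and no denominator or comparison population is fixed. The randomised contrast is valid for adding AI exercises to TAU, but it cannot attribute a gain to AI over and above more practice, so the objective and the Discussion opening overstate what can be concluded.

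The size cannot be computed from the protocol. Under the assumed values, equal acceptance is compatible with a count ratio of 1.0 to 2.0, and zero AI-specific effect with a between-arm difference of about 0.06 to 0.50 SD. These ranges rest on assumed offers, completion, gains and extra volumes.

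The primary analysis is not affected. The change is worth making because it alters what may be claimed.

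**What to change.** 1. **H4.** Remove the inference from uptake to acceptance. Report uptake as the share of offered AI exercise sets completed. Draw acceptance from the System Usability Scale, the student evaluation and the group feedback already in Table 1.
2. **Exercise volume.** Report total volume and conventional volume (total minus AI), Cluster Type A versus B, in the class-level model. Present this as a separate randomised question: does adding AI raise total practice, or displace conventional practice? It is not a test of acceptance, because the supply difference between arms remains. Student-reported volume is the safer source, since transcript upload is described only for AI exercises.
3. **Objective.** In the Background and the opening of the Discussion, reword to *adding AI exercises to TAU compared with TAU alone*. State that the trial does not compare AI with an equal volume of conventional practice.

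Table 1 already lists the volume, usability, evaluation and feedback measures; the share in item 1 also needs the number of AI sets released in each class. The primary analysis stays as planned. The cost is rewording, a short additional analysis and a narrower claim.
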